#### The screening group

This group consists of women without symptoms and/or with a negative test for SARS-CoV-2 during the current pregnancy. These women are recruited at participating centres during their antenatal care check-up or during their visit to the maternity unit.

A woman in the screening group may be included into the COVID-19 group later on during the pregnancy if she contracts COVID-19. This may also be the case at the time of statistical analyses, in case the biobank specimens should indicate an asymptomatic SARS-CoV-2 infection or a positive test result is found registered in the Swedish Register for mandatory registration of notifiable infectious diseases (SmiNet).

### Biological samples from women and newborns

Table 1 describes the maternal and newborn biological samples that are collected prospectively within the COVID-19 in Pregnancy and Early childhood biobank (COPE biobank). Samples are either sent to local hospital laboratories or to the hospital’s biobank facility. Blood samples, liquor samples, amniotic fluid and urine are spun and aliquoted into 225 µL wells. Swabs are frozen in primary tubes and breast milk is vortexed and aliquoted into 0.5 mL wells. Samples are frozen at −80°C within 6 hours. For samples obtained off-hours, these are spun or vortexed, redistributed into secondary tubes and stored in a refrigerator overnight but frozen within 24 hours at the latest. Samples are only thawed directly prior to analysis.

**Table 1 T1:** Maternal and newborn biological samples in the COVID-19 in Pregnancy and Early childhood biobank (COPE biobank)

**Time point**	**Sample**
**COVID-19 group—mothers**	
Antenatal screening	Pre-existing samples taken as part of routine antenatal care and screening. More details under ‘biological samples from women and newborns’.
On being diagnosed with SARS-CoV-2 infection	Nasopharyngeal and pharyngeal swabs or saliva
	Blood 30 mL
	Vaginal swab
	Rectal swab
	Urine 10 mL
At delivery or in case of pregnancy loss/termination of pregnancy	Nasopharyngeal and pharyngeal swabs or saliva
	Blood 30 mL
	Placenta, 12 pieces, in total approximately 10–15 cm^3^
	Vaginal swab
	Rectal swab
	Urine 10 mL
	Placenta/membrane swab (in case of COVID-19 within 14 days before delivery or COVID-19 diagnosis up to 2 days after delivery)
In case of Caesarean section	Amniotic fluid 10 mL
In case of spinal anaesthesia, e.g. at caesarean section	Cerebrospinal fluid 5 mL
At 48–96 hours follow-up post partum	Breast milk 5–10 mL
Follow-up within 12 months post partum	Blood 10 mL
	Breast milk 5–10 mL
**COVID-19 group—children**	
At birth	Umbilical cord blood 7 mL In case of stillbirth: Nasopharyngeal and pharyngeal swabs or saliva and blood 5 mL from heart puncture. These samples are routinely performed as standardised clinical practices in case of stillbirth.
Within 12 hours of delivery	Nasopharyngeal and pharyngeal swabs (in case of maternal COVID-19 within 14 days before delivery or COVID-19 diagnosis up to 2 days after delivery)
48–96 hours post partum	Nasopharyngeal and pharyngeal swabs
	Rectal swab
	Blood 5 mL (in case of maternal COVID-19 within 14 days before delivery or COVID-19 diagnosis up to 2 days after delivery)
Follow-up within 12 months post partum	Blood 5 mL
**Screening group—mothers**	
Antenatal screening	Pre-existing samples taken as part of routine antenatal care and screening. More details under ‘biological samples from women and newborns’.
Follow-up antenatal screening	Blood 30 mL
Delivery	Blood 30 mL
	Nasopharyngeal and pharyngeal swabs or saliva
	Placenta in a subgroup of women as controls, 12 pieces, in total approximately 10–15 cm^3^
A subgroup of women in the screening group (n=30) are sampled according to the COVID-19 group protocol as ‘controls’	
**Screening group—children**	
At birth	Umbilical cord blood 5 mL (plasma) and 1.5 mL (cells). In case of stillbirth: nasopharyngeal and pharyngeal swabs or saliva and blood 5 mL from heart puncture. These samples are routinely performed as standardised clinical practices in case of stillbirth.
A subgroup of newborns in the screening group (n=30) are sampled according to the COVID-19 group protocol as ‘controls’	

COPE, COVID-19 in Pregnancy and Early Childhood.

Samples will be analysed with real-time PCR (RT-PCR) for SARS-CoV-2, serology for SARS-CoV-2 along with other immunological analyses that will be specified according to up-to-date techniques pertinent to SARS-CoV-2 infection.

Pre-existing samples taken as part of routine antenatal care and screening will be obtained from already-existing biobanks along with the newly established COPE biobank. As part of routine antenatal care in Sweden, all women provide a blood sample that is used to screen for hepatitis B, syphilis, rubella and HIV infection in early pregnancy. These samples are stored in Hospital biobanks, according to the Swedish Biobanks Medical Care Act (https://biobanksverige.se/english/research/). For women and children included in the study, these samples may be analysed for serology for SARS-CoV-2 in order to define the time point for an asymptomatic SARS-CoV-2 infection. Similarly, in some centres in Sweden, blood samples from routine testing for immunisation at gestational week 28 are stored and may be analysed for serology for SARS-CoV-2. Further, we plan to combine already existing pregnancy biobanks that have biosamples from different gestational weeks (IMPACT study, dnr 2018-231 (http://www.impactstudien.se/), Uppsala/Örebro; GO PROVE, dnr 955-18, Gothenburg; UPMOST, dnr 2019-00309, Uppsala/Örebro and Biobank för gravida kvinnor, Uppsala, dnr 2007-181, Uppsala/Örebro) with the COPE biobank. These already existing biobanks will provide blood samples collected from February 2020 onwards.

### Register and medical record data on obstetric, medical and neonatal outcomes

Biobank laboratory analyses and questionnaire results will be linked to register data using Swedish personal identification numbers in order to follow long-term maternal and child health as well as child growth and development.

Data will be linked to national quality registers, for example, data on pregnancy outcome, neonatal health or maternal intensive care unit admission (Swedish Pregnancy Register (SPR), Neonatal Quality Register (SNQ) and Intensive Care register), registers from the National Board of Health and Welfare, for example, data on long-term child health (National Patient Register, National Cause of Death Register, Prescribed Drug Register), Statistics Sweden, for example, data on education and income (Register of Total Population, Education Register and Income Register, LISA register), Public Health Agency, data on time point for testing positive for SARS-CoV-2 (Swedish Register for obligatory registration of notifiable infectious disease; SMiNet), growth data during childhood (the Swedish Child Health Care Register) and medical records for additional data, for example, cardiotocography during delivery. The registers are described in detail in box 1.

Box 1Swedish national health and quality registers that will be linked to the COVID-19 in Pregnancy and Early Childhood dataset (COPE dataset)The Swedish Pregnancy RegisterA certified national quality register initiated by the Swedish healthcare regions that combines prospectively collected data from the Swedish Maternal Health Care Register, the Swedish National Quality Register for Prenatal Diagnosis and data from electronic, standardised, prenatal delivery and neonatal records. The register includes more than 95% of all deliveries in Sweden and covers pregnancies from the first antenatal care visit until the follow-up visit at 8–12 weeks post partum. It contains information on maternal characteristics, medical and reproductive history, pregnancy examinations, delivery outcomes and follow-up^41^ (http://www.graviditetsregistret.se/).Examples of variables that will be extracted: pregnancy loss after first visit to antenatal care, body mass index at booking visit, weight gain during pregnancy, gestational age at delivery, mode of delivery, postpartum blood loss, birth weight, Apgar score and pregnancy complications such as gestational hypertension, pre-eclampsia and gestational diabetes.The Swedish Neonatal Quality RegisterA national quality register for neonatal care. All neonatal departments in Sweden report standardised data on admitted infants including basic information about pregnancy and childbirth, as well as the condition, treatment and diagnoses of the infant according to the Swedish version of International Classification of Diseases 10th revision (ICD-10), as well as information from follow-up visits. During the COVID-19 pandemic, all children born to mothers testing positive for SARS-CoV-2 are registered in the Swedish Neonatal Quality Register^42^ (www.snq.se).Examples of variables that will be extracted: admission to neonatal intensive care unit (NICU) or neonatal special care (NSC), duration of NICU/NSC stay, mechanical ventilation, asphyxia related complications, hypothermia treatment.The Swedish Intensive Care RegisterA Swedish quality register on intensive care. Data regarding severity of disease and interventions will be retrieved from Swedish Intensive Care Register for women requiring care at an ICU (http://www.icuregswe.org/).Examples of variables that will be obtained: duration of stay, mechanical ventilation, extracorporeal membrane oxygenation.The National Patient RegisterA mandatory health register including diagnoses on hospital admissions and outpatient visits in specialist care. Information will be retrieved on ICD-10 diagnoses and interventions for women during pregnancy and the postpartum period, chronic or previous disease in the mother as well long-term follow-up of their children^43^ (https://www.socialstyrelsen.se/statistik-och-data/register/alla-register/patientregistret/).Examples of variables that will be extracted: ICD-10 diagnosis of COVID-19 or diagnosis of thromboembolism for the mother during pregnancy as well as 3 months postpartum, diagnosis of neuropsychiatric disease during childhood.The National Cause of Death RegisterThe national cause of death register is based on the obligatory death certificates that need to be signed by a medical doctor confirming the cause of death in the deceased. Both the date and cause of death are registered.(https://www.socialstyrelsen.se/statistik-och-data/register/alla-register/dodsorsaksregistret/)Examples of variables that will be extracted: Time point and cause of death for mothers in the study population until 42 days after delivery, time point and cause of neonatal deaths.The Swedish Prescribed Drug RegisterA mandatory register holding data on all prescribed substances, Anatomical Therapeutic Chemical classification-code and date of purchase, for all dispensed drugs in the outpatient population.^44^
Examples of variables that will be extracted: antibiotics prescribed to children during the first year of life.The Swedish Register for mandatory registration of notifiable infectious disease (SmiNet)COVID-19 is classified as a notifiable infectious disease. All positive SARS-CoV-2 tests are reported to SmiNet by the laboratories analysing the tests as well as the medical doctor responsible for sampling (https://www.folkhalsomyndigheten.se/smittskydd-beredskap/overvakning-och-rapportering/sminet/).Variables that will be extracted: Date for positive SARS-CoV-2 test or date of COVID-19 disease during pregnancy.The Swedish Child Health Care RegisterA national quality register on child healthcare (http://bhvq.se/).Variables that will be extracted: length and weight at 3, 4 and 5 years of age.Statistics SwedenStatistics Sweden is a government agency collecting data on education and income (https://www.scb.se/en/).Variables that will be extracted: family income, education level of the study participants, child school grades.

### Questionnaires

On inclusion, women and their partners from both the COVID-19 group and the screening group, are asked to fill out different electronical questionnaires up to 4 years after delivery. Questionnaires include questions specifically developed for the COPE study as well as validated surveys in order to test for differences between the two groups. Questions developed specifically for COPE have been translated into English, Arabic and Somali. Questions based on validated surveys are provided in other languages only if there is a validated version available.

### Patient-reported outcome measures

Participants are asked about COVID-19 related symptoms, COVID-19 in household members, their work situation, physical activity, the general impact COVID-19 has had on their lives and how they experience social isolation. Further, validated questions from the Gothenburg Research Programme on pregnancy and politics concerning study participants’ opinion on the healthcare sector and authorities during the pandemic^31^ and free-text questions are also asked. Free-text answers will be analysed using content analysis methodology.^32^ Based on validated questionnaires, the study participants are asked to rate their self-efficacy, health-related quality of life, sense of coherence, anxiety/depression, childbirth experiences, levels of breastfeeding self-efficacy, parent–infant bonding, symptoms of post-traumatic stress, self-esteem, perceived stress and attachment style. For details, see table 2.

**Table 2 T2:** Overview and time frame of data sampling by questionnaires

Questionnaire time point	Mother	Other parent
Inclusion (pregnancy), approximately 20 min	GSE*†, HADS*†, SOC*†, EPDS*†, EQ5D-VAS*†	
	COPE questionnaire*†‡: Demographic variables, COVID-19 symptoms, physical activity, subjective experiences and free-text option	
1-week post partum, approximately 5 min	COPE questionnaire: hospital stay, COVID-19 symptoms, hygiene measures etc.*†‡	
1, 2, 3, 4, 5, 6 weeks post partum, approximately 5 min	COPE questionnaire: Morbidity-Q*†‡ At 6 weeks also COVID-19 symptoms	
8–12 weeks post partum, approximately 30 min	CEQ*, BSES*, EPDS*†	FTFQ*
	HADS*†, PBQ*, SQ-PTSD*, EQ5D-VAS*†	
	COPE questionnaire*†‡: demographic variables, COVID-19 symptoms, physical activity, subjective experiences and free-text option	
4 months (corrected age), approximately 10 min	ASQ*	
9 months (corrected age), approximately 10 min	ASQ*	
10 months post partum, approximately 25 min	CEQ*	
	GSE*†, HADS*†, SOC*†, SQ-PTSD*, EQ5D-VAS*†	
	COPE questionnaire*†‡: demographic variables, physical activity, subjective experiences and free-text option	
12 months (corrected age), approximately 10 min	ASQ*	
2 years post partum, approximately 25 min	ASQ*	
	HADS*, RSES*, PSS*, EQ5D-VAS*, ECRS* COPE questionnaire: demographic variables	
3 and 4 years post partum, approximately 25 min	ASQ*	
	HADS*, RSES*, PSS*, EQ5D-VAS* COPE questionnaire: demographic variables	

*Available in English.

†Available in Arabic.

‡Available in Somali.

ASQ, Ages and Stages Questionnaire-Version III; BES, Breastfeeding Self-Efficacy Scale; CEQ, Childbirth Experience Questionnaire; COPE, COVID-19 in Pregnancy and Early Childhood; ECRS, Experiences in Close Relationsships Scale; EPDS, Edinburgh Postnatal Depression Scale; FTFQ, First Time Fathers Questionnaire; GES, General Self-Efficacy scale; HADS, Hospital Anxiety and Depression Scale; PBQ, Postpartum Bonding Questionnaire; PSS, Perceived Stress Scale; RSES, Rosenberg Self-esteem Scale; SOC-13, 13-item Sense of Coherence Scale; SQ-PTSD, Screen Questionnaire - Post-Traumatic Stress Disorder; VAS, Visual Analogue Scale.

### Parent-reported infant morbidity and development

A weekly, web-based child morbidity questionnaire is sent out to parents during the first 6 weeks after delivery. Symptoms of infection (fever 38.0°C or more), abdominal, airway and other symptoms (otitis, rash, excessive crying, tiredness), visiting a doctor, prescription of antibiotics or whether the child has been admitted to hospital are noted. The questionnaire has previously been used in two other Swedish studies.^33 34^

At 4, 9 and 12 months (corrected age) along with 2, 3 and 4 years of age, parents report their infant’s development based on the validated Ages and Stages Questionnaire (ASQ)-version III^34–36^ (see table 2).

### Interviews: women’s and their partners’ experiences of pregnancy, childbirth and postnatal care during the COVID-19 pandemic

Informants will be approximately 12–20 women who were diagnosed with COVID-19 during pregnancy and their partners, as well as 12–20 women and partners who were not diagnosed with COVID-19. Participants will be selected to ensure a broad range of views and experiences, for example, age, parity and socioeconomic background including severity of symptoms in the COVID-19 group. The women and their partners will be interviewed separately using face-to face interviews or by video link or telephone. Open-ended questions with follow-ups will be asked to deepen the understanding.^32^ Interviews will last approximately 1 hour, and will be audiotaped and transcribed verbatim. Data analysis will be conducted using either phenomenology with a lifeworld approach^37^ or by using content analysis.^32^

## Data processing and analysis

### Research questions

The COPE study is collecting information for a database and biobank in order to study the association of COVID-19 during the pregnancy with a wide variety of different pregnancy, maternal and neonatal outcomes including the long-term follow-up of maternal and child health, as well as parental experience.

Predefined research questions concern the incidence of infection and COVID-19 at different time points of the pandemic; the impact of COVID-19, gestational age at infection, severity of disease, viral load, presence of SARS-CoV-2 and/or antibodies against SARS-CoV-2 in different compartments of the mother and/or child, pregnancy outcome, maternal and child health; experience of childbirth and early parenthood during the pandemic (see online supplemental material 2 for details).

10.1136/bmjopen-2021-049376.supp2Supplementary data

### Exposure definition in regard to clinical outcomes

Based on RT-PCR and serology and data from SmiNet, women will be divided into infected women (COVID-19 during pregnancy) and non-infected women (no COVID-19 during pregnancy). In some analyses/subanalyses, gestational age at infection, severity of disease, viral load and immune response will be considered as additional exposure variables for the infected group.

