## Methods and analysis

### Study design and population

The COVID-19 in Pregnancy and Early Childhood (COPE) study is an ongoing Swedish multicentre study, facilitated by the Swedish network for national clinical studies in Obstetrics and Gynaecology (SNAKS, https://www.snaks.se/). Data are collected in four different ways: (1) biosampling, (2) survey-based follow-up until 4 years after delivery, (3) linkage to Swedish health and quality registers enabling long-term follow-up and (4) interviews. All Swedish maternity units with their corresponding neonatal care units have been invited to participate in the study. Centres can participate in the biobank and/or the questionnaire part of the study. So far, 27 maternity units corresponding to more than 87 000 of the approximately 114 000 deliveries per year in Sweden are participating in the study (online supplemental material 1).

10.1136/bmjopen-2021-049376.supp1Supplementary data

Patient recruitment formally started on 1 June 2020. All women, aged 18 years or older, receiving antenatal care or giving birth at participating centres are eligible for the study. Study information and questionnaires have been translated into the most commonly spoken languages in Sweden (Swedish, English, Arabic and Somali). A prerequisite for participation in the interview part of the study is adequate Swedish or English language skills.

Participants have access to study information which is freely available in the waiting rooms of the antenatal care and maternity units involved in the study, the COPE study homepage (www.copestudien.se), social media, interviews and articles available in mass media along with active recruitment by the local study research team.

Recruitment of pregnant women may occur at different time points during the pregnancy, for example, during the first or second trimester ultrasound screening visit, on admission for pregnancy complications or admission to the delivery/COVID-19 units of any of the participating hospitals.

Partners aged 18 years or older are also eligible for participation. Participating women and their partners receive oral and written information about the study and are required to provide written consent. Women can choose to participate in either the biobank or the questionnaire part of the study, or both.

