#### The COVID-19 group

This group includes women that (1) test-positive for SARS-CoV-2 during pregnancy or at delivery, (2) have a positive SARS-CoV-2 antibody test from infection during the current pregnancy or (3) have COVID-19 as a ‘clinical diagnose’ at the time point of delivery before test results are available.

Before June 2020, there was limited testing capacity in Sweden and only symptomatic patients admitted to the hospital were tested. Since June–July 2020, testing for SARS-CoV-2 has become widely available, even outside hospitals, to all citizens in Sweden. In the beginning of 2021, SARS-CoV-2 screening was introduced for all patients admitted to Swedish hospitals including pregnant women on admission to maternity units. All adults, including pregnant women, are currently required to take a SARS-CoV-2 test in case of symptoms. Detailed data on the number of performed tests and test-positivity in different regions, age groups and over time are available at the homepage of the Public Health Agency of Sweden.^30^ Due to restrictions on research-related appointments during the pandemic, women are recruited to the COVID-19 group when they seek inpatient care or in connection with their routine antenatal care visit. In the later case, they are included when they are in remission from COVID-19.

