### Sample size calculations

This is an exploratory study where the initial sample size for recruitment is set to 200 women in the COVID-19 group and 1000 in the screening group (with an additional 10%–15% with assumed positive tests in the screening group thus more than 300 COVID-19 cases). Sample size has been calculated with 80% power and a significance level of <0.05 based on the assumptions shown in table 3. As outcomes are retrieved from population-based registers, there will be close to complete follow-up.

**Table 3 T3:** Assumptions for power calculation

Outcome	Prevalence in screening group	Prevalence in COVID-19 group	Sample size screening group	Sample size COVID-19 group
Pre-eclampsia	6%	12%	511	256
Thrombosis	0.13%	2%	613	306
Small for gestational age (below 10th percentile)	10%	20%	199	199
Preterm delivery	6%	12%	511	256
Neurological and/or neurodevelopmental disorders	1%	4%	581	290

The percentage of women with vertical transmission secondary to active COVID-19 at the time of delivery (14 days before to 2 days after delivery) will be calculated.

Depending on the prevalence of malformations, the presence and type of malformations in case of infection during early pregnancy will be presented in a purely descriptive manner.

The presence of antibodies in umbilical cord blood and breast milk will be studied in relation to gestational week of infection, severity of infection and maternal serum antibody levels. Antibody levels will be followed over time.

Due to the unprecedented nature of the pandemic, it is difficult to perform formal power calculation with regard to parent health and mental well-being.

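### The main exposure contrast splits women into ever and never infected over the whole pregnancy, which mixes immortal time and wrong-order events into preterm delivery and, less so, pre-eclampsia and thrombosis; net direction uncertain

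*Protocol article*

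**What the plan says.** The section on exposure definition says that, from RT-PCR, serology and SmiNet data, "women will be divided into infected women (COVID-19 during pregnancy) and non-infected women (no COVID-19 during pregnancy". Timing appears only in the next sentence: in some analyses or subanalyses, "gestational age at infection, severity of disease, viral load and immune response will be considered as additional exposure variables for the infected group".

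The design sections let both infection and inclusion fall anywhere in pregnancy:

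- Study design and population: "Recruitment of pregnant women may occur at different time points during the pregnancy". The examples run from the first-trimester ultrasound to admission for complications or delivery.
- The COVID-19 group: a first positive test at delivery qualifies. Women may be recruited as inpatients or at a routine antenatal visit; for routine visits, "In the later case, they are included when they are in remission from COVID-19". Testing of all hospital admissions began in early 2021.
- The screening group: "A woman in the screening group may be included into the COVID-19 group later on during the pregnancy if she contracts COVID-19". Of the move between groups it adds: "This may also be the case at the time of statistical analyses".

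General statistical methodology names χ² or Fisher tests for categorical variables, plus unadjusted and adjusted regression. Table 3 sizes the study on group prevalences. Box 1 lists, from SmiNet, "Date for positive SARS-CoV-2 test or date of COVID-19 disease during pregnancy", and gestational age at delivery from the Swedish Pregnancy Register.

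**The concern.** The printed definition assigns exposure with knowledge of the whole pregnancy and applies it from the start. No passage counts time before infection as unexposed, aligns the comparator by gestational week, or requires infection to precede the outcome. Three problems follow.

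1. **Immortal time.** A woman has to remain pregnant until she is infected. Early deliveries have less time in which to become exposed.
2. **Impossible outcomes.** A woman first infected at 37 weeks or later cannot deliver preterm, yet she counts in the infected denominator.
3. **Wrong order.** Pre-eclampsia or thrombosis already present when a woman first tests positive on admission counts as an event in the infected group, because the ICD-10 outcome definitions set no order.

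Preterm delivery is the outcome most exposed to this. Pre-eclampsia and thrombosis are affected chiefly through order, and child outcomes to 4 years little or only indirectly. A reader of the results could not tell how much of an observed risk ratio comes from infection and how much from the way the groups were formed.

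**Working it through.** **Table 3 first.** Preterm delivery, 6% against 12%, two-sided 5%, 80% power, allocation r = 0.5 (pooled variance, no continuity correction):

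n₁ = [1.960·√(p̄q̄(1+1/r)) + 0.842·√(p₁q₁ + p₂q₂/r)]² / (p₂−p₁)², with p̄ = (0.06 + 0.5×0.12)/1.5 = 0.08.

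n₁ = [1.960×0.4699 + 0.842×0.5173]² / 0.0036 = 511.0. This matches the printed 511/256. The table's arithmetic is sound; the issue is what the two groups contain.

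**Null comparison.** Inputs:

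- From the article: 6% preterm.
- Assumed: no effect of infection; constant infection hazard λ; preterm births spread exponentially below 37 weeks with a mean of 2.5 weeks (mean delivery week 34.5); term births around week 40; 10% infected over 40 weeks, so λ = −ln(0.90)/40 = 0.002634.

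Followed from week 0:

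- P(infected | preterm) = 1 − exp(−λ×34.5) = 0.0869; P(infected | term) = 1 − exp(−λ×40) = 0.1000.
- Preterm risk, infected: 0.06×0.0869 / (0.06×0.0869 + 0.94×0.1000) = 0.0525.
- Preterm risk, non-infected: 0.06×0.9131 / (1 − 0.0992) = 0.0608.
- Risk ratio: 0.0525/0.0608 = 0.86.

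Simulating 4 million pregnancies gives about the same and changes little between 10%, 15% and 25% cumulative infection:

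| Infection possible from | Risk ratio (true value 1.00) | Infected women first infected at ≥37 weeks |
|---|---|---|
| Week 0 | about 0.86 | 6% to 7% |
| Week 12 | about 0.80 | 9% to 10% |
| Week 20 | about 0.73 | about 14% |

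**Delayed inclusion of infected women.** With infection weeks uniform over 8 to 40, the infected preterm risk is 5.1%. It falls to 5.0% to 4.8% if women must still be pregnant 2 to 6 weeks later (ratios 0.83 to 0.80 against 6%). The lag is an assumption and concerns only women recruited at routine visits.

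**The opposite push.** If screening women are included at a uniform week between 12 and 40 while still pregnant, preterm births are under-represented among them. The chance of inclusion is (34.5−12)/28 = 0.80 for preterm and about 0.98 for term, so their preterm risk is 0.06×0.80 / (0.06×0.80 + 0.94×0.98) ≈ 5.0%. Infected women recruited at delivery, with the full 6%, then show a null risk ratio of about 1.21. Testing at complication admissions pushes the same way.

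**Does time alignment remove it?** In the same simulation, followed from conception, infected women were compared, week by week, with women still pregnant and not yet infected in that week. The null ratio was 0.99 to 1.01. Restricting comparators to women never infected at any time gave 0.96 to 1.00, so some bias can remain.

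**Power, as a scenario only.** If a true 12% were shrunk by 0.86 or 0.80, it would show as 10.3% or 9.6%. Power would be 57% or 45% at 511/256, and 71% or 57% at 1000/300 (where it starts from 90%).

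**The case against.** - **Unseen detail.** The methods section is headed as general, and it says regression without naming a model. A reader might infer that ordinary regression is fixed; it is not, and a time-varying model is not excluded. That part of the objection stands. What is fixed is the ever/never split, and a time-aligned analysis would have to replace it.
- **Timing is considered.** It is, but only among infected women. Non-infected women have no gestational age at infection, so this cannot align the comparator.
- **Direction.** A reader might infer that infection will look protective, or that a true doubling will be hidden. The documents do not support that. Screening women also enter late, and admission testing and recruitment at complications or delivery push the ratio upward.
- **Power.** A reader might infer a definite loss, for example to 0.65, 0.45 or 0.25 at 511/256 if 10%, 20% or 30% of infected women were first infected at term. The article gives no such shares. Table 3 labels 12% as the prevalence in the COVID-19 group, which may already include term infections, so the dilution could be counted twice. The planned totals (1000, and more than 300 cases) also exceed 511/256.
- **Scope.** The remission rule does not cover inpatients or screening women who convert. Pregnancy loss appears only as an extractable variable in Box 1, and small for gestational age is not a survival-to-infection problem in the way preterm birth is. The point should not be stretched to either.
- **Severity.** The study is declared exploratory and has no confirmatory primary test. This stands and lowers the grade.

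**Conclusion.** The point holds, at should-fix. Followed as printed, the exposure definition gives a contrast for preterm delivery that departs from 1.00 with no effect of infection. Pre-eclampsia and thrombosis are affected to a lesser extent. The illustrated size is a null risk ratio of about 0.86 from week 0 or 0.80 from week 12, against about 1.21 from late screening entry with recruitment of infected women at delivery. These figures rest on the assumed constant hazard, spread of preterm births and uniform inclusion weeks. They show that either direction is possible and do not predict the net bias in this cohort. Moving a woman between groups does not cure the problem unless her time before infection counts as unexposed.

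**What to change.** **Preterm delivery.** Replace the ever/never contrast with an analysis on the gestational-age scale: delayed entry at the week of inclusion, infection as a time-varying exposure (unexposed before the positive-test date), and censoring at 37+0. Alternatively, match each infected woman to enrolled women still pregnant and not yet infected at her week of infection, or at her week of inclusion if that came later. Comparators should not be disqualified by a later infection.

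**Pre-eclampsia and thrombosis.** Count an event as exposed only if infection came before the diagnosis, where a date exists. Otherwise run a sensitivity analysis that excludes women first positive at the delivery or complication admission.

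**Cost.** Positive-test dates and gestational age at delivery are already extracted, so for preterm delivery this is mainly a change of analysis wording. There are three downsides:

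- Serology-only cases have only an interval for the infection date and need a sensitivity analysis. The sample-size section expects cases from within the screening group ("with an additional 10%–15% with assumed positive tests in the screening group"), which is 100 to 150 of 1000; how many would be serology-only is not stated.
- Box 1 lists no onset date for pre-eclampsia, so dates may have to come from the National Patient Register or medical records.
- Women included only at the delivery admission contribute no follow-up under delayed entry, which reduces the number analysed for preterm delivery.
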